#### Secondary outcome measures

2.7.2

(1)Neurophysiology. Rest-state EEG will be collected immediately before and after NITESGON (T0) and will be correlated with the recall of the word-association task 7 (T1) and 28 (T2) days after NITESGON.(2)TES Adverse events*.* We will use the NITESGON exit questionnaire developed by Brunoni et al. [21] to assess potential side-effect (headache, neck pain, scalp pain, tingling, itching, burning sensation, skin redness, sleepiness, trouble concentrating, mood changes) at the end of T0.(3)Blinding. At the end of the experiment (T2), subjects will be asked if they thought they were assigned to the control or active group.(4)Control assessments. We will collect the California Verbal Learning Test II, Delis Kaplan Color Word Interference Test, Beck Depression (BDI) and Anxiety Inventory (BAI), Trial A & B, COWAT and DIGIT Span to verify that the effect obtained cannot be associated due to differences between groups on these control measures. These will be collected during visit 1 before NITESGON (T0), and 28 days after NITESGON (T2).

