### Safety

2.8

Transcutaneous electrical stimulation (tES) is a method that has been used in various clinical populations, including pain, Parkinson's disease, movement disorders, motor strike, aphasia, multiple sclerosis, epilepsy, disorders of consciousness, Alzheimer's disease, tinnitus, depression, schizophrenia, substance abuse, addiction, and craving [22]. Based on a previous review, there is currently no evidence of irreversible injury produced by conventional tES protocols using a wide range of stimulation parameters (≤40 min, ≤ 4 mA, ≤ 7.2 C) [23]. Furthermore, most adverse effects are mild and disappear soon after stimulation [24]. Another paper that summarizes 567 tES sessions over motor and non-motor cortical areas (occipital, temporal, parietal) revealed that according to the present safety guidelines, tES is associated with relatively minor adverse effects (including headache, itching or tingling sensation) in healthy humans and individuals with various neurological disorders [25]. To date, no significant differences in side effects have been observed after receiving active NITESGON compared to sham NITESGON [15,16,26].

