### Sample size

2.9

The study is designed to give us adequate power to detect clinically meaningful differences between the groups. We plan to oversample to a target sample size of 25 subjects per group, with an overall sample of 100 subjects, to assure that our power to detect effects is maintained.

Nineteen individuals per group (total n = 76) would offer us a power of 90% to detect the difference between groups using Cohen's d estimation of a medium effect size (0.20). A sample size of 76 would allow us to see a medium effect size, however the trial is longitudinal which could increase its drop-out rate. Although we do not expect attrition to be large, we expect a dropout rate of no more than 20%. Therefore, an overall sample of 100 subjects will assure enough power to accommodate for the expected drop-out rate.

An intention-to-treat and per-protocol analysis will be performed. For the intention-to-treat analysis, the patient must successfully complete T0 and T1 assessments. For missing observations, the LOCF approach will be used. Exclusion from the population will be finalized prior to database lock in a blinded manner.

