*TES Adverse events.* A comparison will be conducted between the active and sham group using a one-way ANOVA with stimulation (active NITESGON vs sham NITESGON) as independent variable and adverse events as dependent variable.

*Blinding.* A Chi-square test will be conducted comparing actual stimulation (active NITESGON vs sham NITESGON) versus participants' expected stimulation (active NITESGON vs sham NITESGON).

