## Discussion

3

ALF is an early pre-symptomatic feature of autosomal dominant Alzheimer's disease, which appear to pre-date other amnestic deficits and underpin subjective memory complaints in AD [29]. Walsh and colleagues found that aMCI subjects showed greater loss of information over 1 week than controls and that delayed memory recall deficits in aMCI subjects appeared to be related to impaired consolidation when controlling for the initial learning [30]. Similarly, we predict that individuals with aMCI will perform significantly worse 7 days after initial learning of the word association task. The objective of the current project is to determine if NITESGON is an effective intervention to improve memory recall and therefore mitigate ALF in individuals with aMCI.

To the best of our knowledge, there have been no trials evaluating the effect of electrical stimulation of the greater occipital nerve on episodic memory in aMCI populations. LC degeneration has been associated with aMCI [7,[10], [11], [12], [13], [14]], with LC neuropathology detectable as early as 10 years before neurocognitive signs [[31], [32], [33]]. Furthermore, NITESGON can upregulate NA through the LC-NA pathway. Therefore, this approach could potentially benefit individuals with aMCI. The secondary outcome measures will examine mechanisms that may underlie the memory effect these populations.

Early identification of disease combined with effective intervention is the optimal strategy to alleviate memory impairments in aMCI subjects and ultimately maintain quality of life. NITESGON has the potential to improve memory recall by mitigating the disruption of memory consolidation in individuals with aMCI. This new memory management system is non-invasive, non-pharmacological, safe, with few adverse side effects, portable and can be readily applied at a reasonable cost. In addition, NITESGON can be implemented in individuals on a variety of different medications that have not been responsive to other treatments.

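### The only stated active-versus-sham comparison of adverse events is a low-powered one-way ANOVA; risk differences per symptom with confidence intervals would serve better

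*Protocol article*

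**What the plan says.** Adverse events are listed among the secondary outcomes in section 2.7.2. An exit questionnaire covering ten symptoms is given once; the list closes with "trouble concentrating, mood changes) at the end of T0".

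The analysis is in section 2.10: "A comparison will be conducted between the active and sham group using a one-way ANOVA with stimulation" (active or sham) as independent variable and adverse events as dependent variable. The article does not say whether the dependent variable is an item score, a symptom count or a total. It gives no alpha, target difference or margin for this comparison.

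Section 2.9 sets a "target sample size of 25 subjects per group, with an overall sample of 100 subjects". Its power statement concerns the difference between groups and does not mention adverse events.

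Three other places bear on the point:

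- Section 2.8 (Safety) closes by saying that to date "no significant differences in side effects have been observed after receiving active NITESGON compared to sham NITESGON", citing earlier studies.
- Section 2.11 (Data management) promises summary statistics for every variable.
- Section 3 (Discussion) says: "This new memory management system is non-invasive, non-pharmacological, safe, with few adverse side effects".

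**The concern.** A two-group one-way ANOVA is a two-sample t-test. With 25 per arm it is sensitive only to large differences, so a non-significant result is likely even when stimulation causes noticeably more side effects than sham. A comparison of means also does not say how many people had a given symptom, which is what a tolerability statement needs.

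Section 2.8 shows that results of this kind are already offered as reassurance. If this trial's result were used in the same way, the statement would extend to people with amnestic mild cognitive impairment without showing how large an excess the data leave open.

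**Working it through.** **The plan's own figure.** None is given for adverse events. The only power figure, 90% with 19 per group (76 in all) at an effect size of 0.20, is for the difference between groups. It can be reproduced as Cohen's f = 0.20 for a group-by-time interaction with 4 groups, 3 time points, an assumed correlation of 0.5 and alpha 0.05: power is 0.901 at N = 76. It does not reproduce as Cohen's d, the label used. The present point does not depend on it.

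**Inputs.**

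- n = 25 per arm (section 2.9).
- Two groups, F-test, hence non-directional (section 2.10). The directional hypotheses in that section concern the behavioural assessment.
- Assumed: alpha 0.05 two-sided, with one-sided 0.05 as the range; an excess of 0.5 SD; one symptom at 30% active against 10% sham.

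**Power for a 0.5-SD excess.** Noncentrality = d × √(n/2) = 0.5 × √12.5 = 1.768, with 2 × 25 − 2 = 48 degrees of freedom.

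- Two-sided, critical t = 2.011: power 0.410, so missed 59% of the time. The normal approximation, Φ(1.768 − 1.960), gives 0.424.
- One-sided 0.05: power 0.539, missed 46% of the time.

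**Power for 30% against 10% on one symptom.** These are exact sums of binomial probabilities over all pairs of counts from 0 to 25, two-sided.

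- ANOVA on 0/1 data: 0.450, missed 55% of the time.
- Fisher's exact test: 0.305, missed 70% of the time.
- One-sided t-test on 0/1 data, for the range: 0.572.

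**If only 20 per arm are analysed.** Section 2.9 allows for up to 20% dropout: 25 × 0.8 = 20. The questionnaire is completed at the end of T0, so all 25 may be available. The intention-to-treat set, however, requires T0 and T1, and the article does not say which set applies to adverse events. At 20 per arm, two-sided power is 0.338 for 0.5 SD; for 30% against 10% it is 0.357 (ANOVA on 0/1 data) or 0.242 (Fisher).

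**What 25 per arm can detect.** Power of 80%, two-sided, needs about 0.81 SD, or about 44% against 10%.

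**What the data can exclude.**

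- Mean difference: 95% half-width = t(0.975, 48) × √(2/25) = 2.011 × 0.2828 = 0.569 SD. An observed difference of exactly zero leaves a 0.5-SD excess inside the interval. The excess is excluded only if the active arm is observed to be better by more than 0.569 − 0.5 = 0.069 SD.
- Risk difference with both arms at 10%: 1.96 × √(2 × 0.1 × 0.9/25) = 0.166, about 17 percentage points either way.
- No events among 25: one-sided 95% upper bound = 1 − 0.05^(1/25) = 0.113, or 11.3%.

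**The case against.** A reader might infer that the plan judges safety by this test, so that a non-significant ANOVA will count as proof of safety. The documents do not support that. Section 2.10 says only that a comparison will be made, and nothing in the article turns its p-value into a safety conclusion. The favourable sentence in the Discussion was written before any data from this trial and cannot rest on this ANOVA. Section 2.8 relies mainly on other evidence: a review that found no irreversible injury, mostly mild and short-lived effects, and a summary of 567 sessions. Its remark on non-significance comes last, concerns earlier studies, and does not name the tests they used.

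A reader might also infer that no incidence will be reported. That goes too far as well. The summary statistics promised in section 2.11 plausibly include symptom counts, although the sentence is generic and commits to no risk difference or confidence interval.

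Other objections stand in part:

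- The alpha and both effect sizes are assumptions. Under a one-sided 0.05 test, power rises just above one half, so the statement that such an excess is missed more often than not holds only for a two-sided test. The ANOVA named in the plan is two-sided.
- The binary figures apply to one symptom. An excess spread over several of the ten would be missed on all of them less often.
- Low power for side effects is usual at this size and contradicts nothing in section 2.9.
- Interval methods and interpretation wording are often left to an analysis plan, which is not shown, so their absence alone is no finding. The ANOVA, however, is a method that the article does state, and it can be judged as stated. The general allowance in section 2.10 for non-parametric tests or transformations would change the test, but it would still give a p-value at the same sample size.

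**Conclusion.** The point holds in a limited form. The one comparative adverse-event analysis in the article is poorly suited to symptom data and has low power: 41% for a 0.5-SD excess and 30% to 45% for one symptom at 30% against 10%, with 25 per arm and two-sided alpha 0.05. Its confidence interval would reach about 0.57 SD either side of the estimate. These sizes rest on an assumed alpha and assumed effects; the interval width does not depend on the assumed effects.

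Non-significance alone would not exclude a material excess of side effects, and section 2.8 shows that such results are already cited as reassurance. The plan makes no such claim for this trial, and the primary outcome is not affected. This is a cheap improvement to the analysis and its reporting, not a fault in the design.

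**What to change.** In section 2.10, replace the ANOVA as the basis of the adverse-event comparison with the following:

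1. For each questionnaire symptom, the number and percentage affected in each arm.
2. For each symptom, the active-minus-sham risk difference with a 95% confidence interval (exact or score).
3. For symptoms with no events in an arm, the upper confidence bound (one-sided 95% bound of 11.3% for none among 25).
4. A sentence stating that a non-significant comparison will not be cited as evidence of no difference.

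The questionnaire already supplies the data, so no participants, visits or procedures are added. The cost is a less favourable statement: the report would give the size of excess that cannot be excluded, rather than say that no significant difference was found.

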### Data management

2.11

All data will be managed using unique study codes, which will be used to code and file all electronic information, to protect participant confidentiality. The key linking these codes to participants' identities will be stored in a secured file. Access to this key will be available only to designated members of the research team at each site. To ensure privacy, all research files will be stored in locked file cabinets in locked offices at Trinity. Electronic information will be stored at a secure, password-protected, server at Trinity and all corresponding data analysis will be conducted at Trinity to ensure central and complete data protection. Subject names will not be published. Summary statistics will be performed on all variables and reported.

## Discussion

3

ALF is an early pre-symptomatic feature of autosomal dominant Alzheimer's disease, which appear to pre-date other amnestic deficits and underpin subjective memory complaints in AD [29]. Walsh and colleagues found that aMCI subjects showed greater loss of information over 1 week than controls and that delayed memory recall deficits in aMCI subjects appeared to be related to impaired consolidation when controlling for the initial learning [30]. Similarly, we predict that individuals with aMCI will perform significantly worse 7 days after initial learning of the word association task. The objective of the current project is to determine if NITESGON is an effective intervention to improve memory recall and therefore mitigate ALF in individuals with aMCI.

To the best of our knowledge, there have been no trials evaluating the effect of electrical stimulation of the greater occipital nerve on episodic memory in aMCI populations. LC degeneration has been associated with aMCI [7,[10], [11], [12], [13], [14]], with LC neuropathology detectable as early as 10 years before neurocognitive signs [[31], [32], [33]]. Furthermore, NITESGON can upregulate NA through the LC-NA pathway. Therefore, this approach could potentially benefit individuals with aMCI. The secondary outcome measures will examine mechanisms that may underlie the memory effect these populations.

Early identification of disease combined with effective intervention is the optimal strategy to alleviate memory impairments in aMCI subjects and ultimately maintain quality of life. NITESGON has the potential to improve memory recall by mitigating the disruption of memory consolidation in individuals with aMCI. This new memory management system is non-invasive, non-pharmacological, safe, with few adverse side effects, portable and can be readily applied at a reasonable cost. In addition, NITESGON can be implemented in individuals on a variety of different medications that have not been responsive to other treatments.
